e One item from the QSU will be used for assessing craving weekly during CM intervention. This has been specified in Table 2.

f Salivary cotinine will be used as needed to resolve the inconsistency between the CO results. Individuals with CO levels >6 ppm, who report smoking cannabis via TLFB and are not taking any formulation of nicotine, salivary cotinine <10 ng/ml will be used.

**Table 2. T2:** Mobile contingency management (mCM) intervention protocol.

mCM components	Week				
	1	2	3	4	5
iCO Smokerlyzer^a^/iCO app training (daily, weekend, and holidays optional)					
iCO Smokerlyzer/CO video uploads (daily, weekends, and holidays optional)					
CM^b^ incentive (daily)					
Behavioral counseling and clinician feedback session (once weekly)	✓	✓	✓	✓	✓
Assessments^c^					
Timeline Followback (TLFB)	✓	✓	✓	✓	✓
Questionnaire of Smoking Urges (QSU)^d^	✓	✓	✓	✓	✓

a The Smokerlyzer (coVita) is a breath carbon monoxide (CO) device that aids smoking cessation by measuring the amount of CO in the breath of a smoker.

b CM: contingency management.

c Assessments (TLFB and QSU) will be administered weekly to assess past 7-day smoking and the level of craving.

d One item from the QSU will be used for assessing craving weekly.

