### Randomization and Blinding

Eligible participants will be randomly assigned to either CM or TAU in a 1:1 ratio, stratified by (1) biological sex and (2) cigarettes per day (≥10 or <10 cigarettes per day) using random permuted blocks via REDCap. We will examine subgroups in exploratory analyses. Due to staffing constraints, no member of the study team will be blinded.

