#### Outcome Measures

##### Smoking Measures

Smoking cessation outcomes will be administered at baseline and posttreatment. A Nicotine and Tobacco Use Survey (NTUS) developed internally will assess age at first use, duration of use, use of all forms of nicotine and tobacco, prior quit attempts (ie, intentionally not smoking for ≥24 h), duration of cessation (if any), and presence of other tobacco users in the home. Posttreatment assessment will include frequency and duration of quit attempts in the past 30 days. The Fagerström Test for Nicotine Dependence (FTND) [39] is a validated instrument of the severity of physiological addiction to nicotine. The Contemplation Ladder [40] is a validated single-item measure of motivation to quit smoking. The Questionnaire of Smoking Urges [41,42] is a validated 10-item measure that assesses cigarette craving and withdrawal. It will also be administered weekly to assess craving via 1 item, *“*I have a desire for a cigarette right now,” via a scale from 0 (strongly disagree) to 100 (strongly agree) [42]. The Timeline Followback (TLFB) [43,44] is a validated, staff-administered instrument that uses anchor dates to prompt recall of substance use. It will be used to document cigarette, tobacco, electronic nicotine delivery system (ie, e-cigarette), cannabis, any other substance uses, and TUD medications. Participants who are in CM condition will be assessed at screening for past 30-day use, at weekly sessions for past 7-day or days since the last TLFB assessment, and at follow-up visit for days since the last TLFB assessment; participants who are in TAU condition will be assessed at screening for past 30-day use and at follow-up visit for days between the last TLFB assessment and follow-up assessment. Bioverification using mobile CO monitor will also be used to verify abstinence at follow-up visit. If there is inconsistency between self-report and bioverified CO level, a salivary cotinine test might be adopted as needed.

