During weeks 2 to 5, the intervention phase, participants will upload videos verifying smoking abstinence at a minimum of once per day and 5 times per week, with weekends and holidays being optional. Abstinence is defined by CO levels ≤6 parts per million (ppm) [47]. An escalating monetary reinforcement schedule for the proof-of-abstinence video uploads will follow a previously published CM protocol [26,27], ranging from US $5 to approximately US $45, adapted to include a nominal incentive for video uploads. The incentive will reset to US $5 following a positive CO reading or missed video upload without a documented excused absence. The salivary cotinine test will be used as needed to resolve inconsistencies between self-reported abstinence and the CO results. Besides monetary reinforcement, clinician feedback will be provided after each CO reading upload, following previously established VA protocols for CM [25]. CO readings will be reinforced with weekly feedback sessions from study clinicians, which will be incorporated into behavioral coaching/counseling sessions. Feedback sessions will be scripted to encourage continued abstinence through nonmonetary positive reinforcement, including assessments of urges/cravings and use behaviors, and expressions of empathy and confidence [25]. Participants can earn approximately US $595 maximum for uploading daily videos throughout 5 weeks and maintaining abstinence from weeks 2 to 5. Compensation rates are approximate and will be raised as needed to account for inflation, aligned with practices recommended by VA CM subject-matter experts at the Center of Excellence in Substance Addiction Treatment and Education.

For participants who are also using noncigarette tobacco or e-cigarettes, abstinence cannot be bioverified. In these instances, participants will be educated about the risks of these products, and their use will be tracked in the TLFB [43,44] but will not determine CM incentives. Technology reluctance is relatively common among older adult outpatients and can be a barrier to telehealth interventions [48]. To promote adherence, we will order a technology-support consult for individuals with identified technology reluctance or technical challenges and will meet with participants until they gain proficiency with video uploads. For those who are unable to upload videos after these efforts, staff will meet via secure video conference to capture and record CO readings on behalf of the participants.

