#### Exploratory Outcomes

Seven-day point prevalence of cigarette abstinence will be assessed post treatment, defined as (1) no smoking for 7 days prior (via TLFB) and (2) CO levels ≤6 ppm. For individuals with CO levels >6 ppm, who report smoking cannabis via TLFB and are not receiving NRT, salivary cotinine <10 ng/ml will be used [47,51]. Cutoffs are recommended by the SRNT (Society for Research on Nicotine and Tobacco) guidelines [47].

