Potential barriers to success may include issues such as technology or internet issues, a high frequency of bioverification, an inability to bioverify for the use of electronic cigarettes and noncigarette tobacco products, and the heterogeneity of the surgical population [48,56]. To mitigate selection bias and attrition, our strategies will include 1 week of training and practice, ordering digital-support consults as needed and video conferencing with staff to obtain CO readings if needed. Additionally, the short half-life of CO poses a challenge to identifying a feasible, outpatient bioverification schedule that confirms daily smoking abstinence. VA protocols for smoking cessation were designed for residential treatment settings, with daily CO monitoring conducted on-site. One challenge of including participants who use smokeless tobacco, e-cigarettes, and other tobacco products is that we cannot bioverify abstinence from these products using CO monitoring. We will focus on smoking cessation bioverification and collect data pertaining to the cessation of other nicotine and tobacco products through TLFB. The CO abstinence verification plan implemented in this CM protocol aims to strike a balance between feasibility and scalability in outpatient settings and specificity in identifying bioverified abstinence from combustible cigarettes only. Our group operationalized the standard definition of smoking abstinence as self-report verified by CO≤6 ppm, as is recommended by SRNT consensus guidelines [47]. The 5-days-per-week, once-per-day CO video upload schedule includes same-day, rapid clinician feedback, which is a critical component of CM [25]. The protocol allows for optional weekend and holiday videos as well, but those videos cannot be reviewed and addressed on the same day due to outpatient staffing. The short half-life of CO and the challenge of demonstrating durable abstinence is an inherent limitation of any smoking cessation CM protocol in which nicotine replacement products are offered to be prescribed (preventing the use of cotinine testing among those prescribed NRT). Once-daily CO monitoring has been considered adequate for most smoking cessation protocols, including those in VA residential treatment programs.

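### The cotinine rule after a failed CO test is optional and broad in some places but mandatory and narrow in the endpoint definition, with unblinded staff choosing when to test

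*Protocol article*

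**What the plan says.** Seven-day point prevalence abstinence is defined under Exploratory Outcomes by two conditions: "1) no smoking for 7 days prior (via TLFB) and (2) CO levels ≤6 ppm". Four statements in the protocol article then say when salivary cotinine comes in.

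- **Smoking Measures** (follow-up visit): "If there is inconsistency between self-report and bioverified CO level, a salivary cotinine test might be adopted as needed". It gives no cutoff, no cannabis condition and no nicotine exclusion.
- **Table 1, footnote f.** First sentence: "Salivary cotinine will be used as needed to resolve the inconsistency between the CO results". Second sentence, for CO above 6 ppm, limits the test to those "who report smoking cannabis via TLFB and are not taking any formulation of nicotine, salivary cotinine <10 ng/ml will be used".
- **Exploratory Outcomes** (the endpoint definition), for CO above 6 ppm: those "who report smoking cannabis via TLFB and are not receiving NRT, salivary cotinine <10 ng/ml will be used".
- **CM Condition: Overview and Timeline** (CM arm, weeks 2 to 5): "The salivary cotinine test will be used as needed to resolve inconsistencies between self-reported abstinence and the CO results".

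Two further statements bear on these. Randomization and Blinding says that "no member of the study team will be blinded". The Discussion names the prescribing of NRT as "preventing the use of cotinine testing among those prescribed NRT". Under TUD Medication Management, NRT is among the medications that can be prescribed at week 0 in both arms, as a 5-week supply.

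**The concern.** A second test that is run only after a failed first test can improve a participant's status but not worsen it. If every eligible participant gets it, it corrects a known false positive of CO, here smoke from cannabis. If staff choose who gets it, and they know the arm, its use can differ by arm, and the abstinence comparison then carries a difference that the treatment did not cause.

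The passages also disagree on who is eligible. A coder who follows Smoking Measures and one who follows Exploratory Outcomes would not send the same people for testing. In addition, NRT is offered to everyone and rules out cotinine, so the plan may leave some true abstainers with no way to be recognised. NRT use is settled after randomization and need not be equal between arms.

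**Working it through.** The plan gives no figure on this point, so there is none to reproduce. The check is to apply the week-6 statements to the same participants and then to scale the result.

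**Step 1: direction.** A participant who reports smoking fails the first condition of the endpoint whatever cotinine shows. A participant who reports abstinence with CO at or below 6 ppm shows no conflict. The only conflict that a cotinine result could change is reported abstinence with CO above 6 ppm, and it could change it only towards abstinent.

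**Step 2: five participants, all reporting 7 days of abstinence.**

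| Participant | Exploratory Outcomes | Footnote f, second sentence | Smoking Measures |
|---|---|---|---|
| A: CO 8 ppm, no cannabis, no nicotine product | Not eligible for cotinine; CO condition failed | Not eligible | May be tested |
| B: CO >6 ppm, cannabis, no nicotine product | Cotinine required | Cotinine required | May be tested |
| C: CO >6 ppm, cannabis, e-cigarette, no NRT | Cotinine required | Not eligible, if the nicotine exclusion covers e-cigarettes | May be tested |
| D: CO >6 ppm, cannabis, on NRT | Not eligible; CO condition failed | Not eligible | May be tested, although the Discussion says NRT prevents it |
| E: CO ≤6 ppm, cannabis, on NRT | Abstinent | Not needed | No conflict |

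A, B and C show that the statements select different people. For A, Smoking Measures opens a test that the endpoint rule does not, and does not say what a low result would mean. For B, one statement makes optional what another requires. C depends on whether the exclusion is NRT or all nicotine; the CM section expects e-cigarette users in the trial. D has no usable route to abstinent status. E does.

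**Step 3: size of one reclassification.** With 36 participants randomized 1:1, each arm has 18 (Power Analysis). One participant changes an arm's rate by 1/18 = 5.6 percentage points.

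**Step 4: illustration with assumed counts.** Take 7/18 against 3/18 abstinent, a difference of 4/18 = 22.2 points (two-sided Fisher p = 0.26). Moving participants from smoking to abstinent in the first arm only gives:

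- one: 8/18 vs 3/18, 27.8 points, p = 0.15
- two: 9/18 vs 3/18, 33.3 points, p = 0.075
- three: 10/18 vs 3/18, 38.9 points, p = 0.035

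The counts are not from the document, and the planned analysis is a mixed model, so this only shows scale.

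**Step 5: how common is participant D?** Share of true abstainers affected = (share smoking cannabis) × (share on NRT at week 6) × (probability that CO is above 6 ppm), treating the factors as independent. The document gives none of the three. With assumed ranges of 10–30%, 30–70% and 25–100%:

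- low: 0.10 × 0.30 × 0.25 = 0.0075, about 0.7%
- high: 0.30 × 0.70 × 1.00 = 0.21, or 21%

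If all 18 in an arm were truly abstinent, that would be 0.1 to 3.8 people; with fewer abstainers it is proportionally less.

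**The case against.** The strongest reply is that the endpoint has one definition and it is firm. Exploratory Outcomes prescribes cotinine for a named subset at a named cutoff, and Smoking Measures merely describes an instrument. That stands in part. A reader might infer that the endpoint itself is discretionary, or that participant A is abstinent under Smoking Measures; neither is supported. The endpoint rule is mandatory for its subset, and Smoking Measures sets a trigger for testing without a cutoff or a classification. But that section speaks of the same follow-up verification and gives the test a purpose, settling a conflict about abstinence, so a low result would invite use. Nothing says that the narrow rule overrides the open one.

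A reader might also infer that abstinent cannabis smokers on NRT are always counted as smoking. The text does not support that. Participant E meets the definition, and the Discussion notes the short half-life of CO, so E is realistic. The week-0 NRT supply lasts 5 weeks and follow-up is at week 6 with up to 14 further days, so some will no longer be on NRT and would then qualify for cotinine. The gap is confined to those still on NRT with CO above 6 ppm. The Discussion does disclose that NRT blocks cotinine; it does not say how these people are coded.

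The weeks 2 to 5 wording in the CM section concerns verification during treatment in one arm. It does not define the week-6 outcome and is no evidence of a conflict in it.

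Finally, the outcome is exploratory, efficacy is expressly unpowered, and a rescue still needs an actual low assay result, so staff cannot reclassify at will. All of this stands and limits the weight of the point. The choice of whom to test remains open to staff who know the arm.

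**Conclusion.** The point holds in a limited form. At week 6 the document gives an optional, broad cotinine trigger (Smoking Measures; footnote f, first sentence) and a mandatory, narrow one (Exploratory Outcomes; footnote f, second sentence), and the two narrow versions differ on the nicotine exclusion. Because nobody is blinded, testing outside the defined subset could raise abstinence unequally by arm.

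Each such participant is worth 5.6 points in an arm of 18. How many there would be is unknown, and no bias has been shown to have occurred. The second, smaller point is that cannabis smokers still on NRT with CO above 6 ppm cannot be classed abstinent. Their share depends entirely on assumed rates (0.7% to 21% of true abstainers over the ranges used).

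Only the exploratory 7-day abstinence outcome is affected. The feasibility outcomes, quit attempts, cigarettes per day and nicotine dependence do not use cotinine. The change is still worth making, because biochemically verified abstinence is a result that readers of this pilot are likely to look at, and the inconsistency is cheap to remove.

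**What to change.** 1. Make the rule under Exploratory Outcomes the single week-6 rule, keeping its cannabis condition and cutoff. Widening the rule to all failed CO tests is not needed and would change the endpoint mid-trial.
2. Align Smoking Measures and footnote f to it: remove *might* and *as needed*, and use one nicotine exclusion everywhere, covering NRT, e-cigarettes and other nicotine products.
3. Run cotinine for every participant who meets the rule, in both arms. Count all other CO above 6 ppm as smoking in the main coding, including any case where an optional test outside the rule was already done.
4. Report by arm the number of self-reported abstainers with CO above 6 ppm, cannabis use and nicotine-product use, and add a sensitivity analysis that recodes them as abstinent.
5. Reconcile the in-treatment cotinine wording in CM Condition: Overview and Timeline with the Discussion's statement about NRT.

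Cost: a few more cotinine samples, one extra analysis and a minor amendment, which under Ethical Considerations means IRB approval, a ClinicalTrials.gov update and submission to the DSMB. No new assay or visit is needed, since Table 1 already lists salivary cotinine at week 6. With 18 of 36 randomized as of May 2026, the rule can be settled before outcomes are analysed.

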##### Nonsmoking Outcomes

The 12-Item Short Form Health Index [45] is a validated measure that assesses multiple domains of health-related quality of life; it will also be assessed at baseline and posttreatment.

### Other Data Documentations

A review of the VA medical record will be completed at baseline and posttreatment by staff, assessing medical conditions and treatment. Surgical complications will also be documented as adverse events (AEs). There are no restrictions on concomitant medical and mental health treatment. Concomitant medical and mental health treatment will be documented for all participants to track participants’ engagement in other interventions, and TAU participants will have their number of sessions in TAU interventions tracked.

### Interventions

#### TUD Medication Management for Both Conditions

A study physician will meet all participants receiving CM and TAU at baseline (week 0) to prescribe a 5-week supply of nicotine replacement therapy (NRT; patch, gum, and lozenge), bupropion, and varenicline, if clinically indicated and desired, following a standard prescribing algorithm [21]. Medication for individuals with TUD is recommended (unless medically contraindicated) but will not be required for study participation.

#### CM Condition: Overview and Timeline

The CM counseling intervention is based on the VA Center of Excellence in Substance Addiction Treatment and Education CM residential treatment protocol for smoking cessation [26,27], adapted in three ways: (1) CM incentives are introduced after 1 week of practice, and the intervention duration is extended (ie, from 4 to 5 wk), (2) mobile CO bioverification is used to address the barrier of requiring frequent in-person visits, and (3) a fixed rather than variable schedule incentive structure is used to enable remote bioverification. The intervention timeline includes week 1 preparation for quit date, week 2 quit date and CM initiation, weeks 3 to 4 CM abstinence reinforcement, and week 5 CM relapse prevention. Table 2 depicts the components in this mCM protocol.

Bioverification will occur through the use of a mobile CO monitor and app (iCO Smokerlyzer, CoVita Bedfont [46]). Participants will upload a daily video of themselves performing the CO test with the given CO monitor to a secure VA platform, for clinical purposes only. iCO devices are intended for personal use only and will be provided to each participant.

During week 1, the training and preparation phase, participants will receive guides and training sessions. They will either use a study iPad provided by research staff or proceed with their own electronic device to record themselves performing the CO test, exhaling into the device and showing the CO reading on camera. The CO video upload will occur once per day, with weekends and holidays being optional. The daily CO video will be uploaded to My VA Images, a secure VA platform, where veterans can share videos and photos securely with staff. Participants will receive US $5 per day for the daily video submission in week 1 irrespective of the CO reading (ie, not contingent on abstinence).

During weeks 2 to 5, the intervention phase, participants will upload videos verifying smoking abstinence at a minimum of once per day and 5 times per week, with weekends and holidays being optional. Abstinence is defined by CO levels ≤6 parts per million (ppm) [47]. An escalating monetary reinforcement schedule for the proof-of-abstinence video uploads will follow a previously published CM protocol [26,27], ranging from US $5 to approximately US $45, adapted to include a nominal incentive for video uploads. The incentive will reset to US $5 following a positive CO reading or missed video upload without a documented excused absence. The salivary cotinine test will be used as needed to resolve inconsistencies between self-reported abstinence and the CO results. Besides monetary reinforcement, clinician feedback will be provided after each CO reading upload, following previously established VA protocols for CM [25]. CO readings will be reinforced with weekly feedback sessions from study clinicians, which will be incorporated into behavioral coaching/counseling sessions. Feedback sessions will be scripted to encourage continued abstinence through nonmonetary positive reinforcement, including assessments of urges/cravings and use behaviors, and expressions of empathy and confidence [25]. Participants can earn approximately US $595 maximum for uploading daily videos throughout 5 weeks and maintaining abstinence from weeks 2 to 5. Compensation rates are approximate and will be raised as needed to account for inflation, aligned with practices recommended by VA CM subject-matter experts at the Center of Excellence in Substance Addiction Treatment and Education.

For participants who are also using noncigarette tobacco or e-cigarettes, abstinence cannot be bioverified. In these instances, participants will be educated about the risks of these products, and their use will be tracked in the TLFB [43,44] but will not determine CM incentives. Technology reluctance is relatively common among older adult outpatients and can be a barrier to telehealth interventions [48]. To promote adherence, we will order a technology-support consult for individuals with identified technology reluctance or technical challenges and will meet with participants until they gain proficiency with video uploads. For those who are unable to upload videos after these efforts, staff will meet via secure video conference to capture and record CO readings on behalf of the participants.

